### Who will take informed consent? {26a}

Prior to baseline visits, written information is mailed to participants and, when scheduling an appointment, oral information is also provided by a study nurse. At baseline visits, the trial is again described orally, and informed consent is obtained by physicians.

### Additional consent provisions for collection and use of participant data and biological specimens {26b}

Not applicable.

## Interventions

### Explanation for the choice of comparators {6b}

It was considered non-ethical to deny patients interested in tapering of opioids the intervention. The study was therefore designed to use waiting list as the control group with a cross-over design receiving intervention after 4 months.

### Information to and screening of all participants before randomization

Written and oral information before baseline visit is provided to each eligible participant on:
The study design and the randomization procedureThe rationale for the study and information on dosages that might cause harm and possible symptoms at withdrawalThe possibility to withdraw consent to participate at any time point with no requirement to motivate the decision

At baseline visits, additional information is provided and screening is carried out.

Topics that are covered during the baseline visit:
The participant’s understanding of his/her long-term non-cancer pain is discussed, and when called for, information is provided.A structured screening of possible opioid-related side effects that the patient might experience is performed.Possible side effects of long-term opioid therapy at the group level as well as reported by the participant are discussed in connection to the patient’s conceptualization of the advantages of the opioid treatment.Evidence-based pharmacological treatments for long-term pain, i.e., serotonin–norepinephrine reuptake inhibitor (SNRI), tricyclic antidepressants, and gabapentinoids.The need for study subjects to, during the trial, give the prescribing physician access to the national register of prescribed medications to follow dispensing of opioids.The participant’s daily intake of opioid converted to milligram morphine equivalent per day (MME) is calculated. If the consumed median daily opioid dose in morphine equivalents exceeds 100 mg, the patient is informed of the increased risks of dangerous overdose and tapering is thus strongly suggested. If benzodiazepines are co-prescribed, tapering of opioids is also strongly suggested.The tapering procedure and possible symptoms of withdrawal that might appear during tapering are described.

#### Screening

The initial part of the evaluation process encompasses a structured interview using DSM-5 substance use disorder criteria, urine drug screening, and blood sampling and analyses of Phosphatidylethanol 16:0/18:1 (B-PEth). Drug screening is performed for detection of morphine, codeine, heroin, oxycodone, buprenorphine, methadone, tramadol, benzodiazepines, cannabinoids, amphetamine, and cocaine with confirmatory testing on the accredited laboratory when unexpected findings occur. A blood test for B-PEth is made to detect levels of alcohol use during approximately the last 2 weeks. Refusal to perform the tests is evaluated as equal to a positive test. Interview, laboratory testing, and clinical judgment are all considered to evaluate the presence of SUD according to DSM-5 criteria [29].

### Intervention description {11a}

After randomization and at the baseline visit, a written individual treatment plan is established by the physician and reviewed by the nurse and participant in concordance with guidelines [27, 30].

The written treatment plan includes the following:
Information on well-known risks and side effects of long-term opioid treatments of long-term pain.Possible symptoms of withdrawal that might appear during tapering.The participant’s daily intake of opioid converted to milligram morphine equivalent dose per day (MME).The participants’ individual goals with tapering opioids.Information about follow-up: weekly follow-up at the commencement of tapering. Nurses’ follow-up is then performed according to participants’ needs which can be weekly or less frequent.The architecture of the tapering process where the participant is advised to decrease the dosage with approximately 5–10% from starting dose every week.The rationale for switching to a single preparation of extended-release opioid preparation if immediate-release opioids are used. If more than one type of opioid is used, tapering is performed with one drug at the time. If the patient is willing to taper pregabalin or benzodiazepines, this may be performed as well.Participant’s approval to prescribing doctor during the trial to use the Swedish drug register of the National Board of Health and Welfare. Opioids are prescribed with 7–30-day intervals or may be delivered by multi-dose dispensing by staff in intervals of 1 or 2 weeks if there are problems in following prescriptions.Information about urine drug screening and blood test for B-PEth that may occur at any time during the trial and should be performed on demand within 48 h. Refusal to perform the test is equal to a positive test. Results on drug screening are delivered approximately 1 week after sampling and are sent by post. If drug screening at baseline is without remark, no more drug screening is performed during tapering.Consequences that may occur if the treatment plan is not followed.The collaborative decision physician–participant on however evidence-based and safe pharmacological treatments for long-term pain, i.e., serotonin–norepinephrine reuptake inhibitor (SNRI), amitriptyline, and gabapentin, is in question to be tested after or during tapering.During tapering, rescue medication may be used. NSAID used for increased pain is and alimemazine, mirtazapine, or equal drug is in question to use for sleeping disturbance.Named contact nurse during the trial.

Follow-up will be performed by a nurse, preferably by phone, but can be made possible in person. Visits are necessary if multi-dose drug dispensing proves necessary. The number of contacts with the nurse is optional and decided by the participant in cooperation with the nurse. During tapering, the nurse may slow down tapering if participants are having problems following the plan or report a considerable decline in health and function.

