**Methods:**

The study is a randomized controlled trial. The sample size was set to a total of 140 individuals after estimation of power and dropout. Participants will be recruited from a population with long-term non-malignant pain who will be randomly allocated to (1) the start of tapering immediately or (2) the control group who return to usual care and will commence tapering of opioids 4 months later. A 12-month follow-up is included.

When all follow-ups are closed, data from the Swedish drug register of the National Board of Health and Welfare will be collected and individual mean daily opioid dose in morphine equivalents will be calculated at three time points: baseline, 4 months, and 12 months after the start of the intervention. At the same time points, participants fill out the following questionnaires: Numeric Pain Rating Scale (NPRS), Tampa Scale of Kinesiophobia (TSK), Pain Catastrophizing Scale (PCS), Chronic Pain Acceptance Questionnaire (CPAQ-8), Hospital Anxiety and Depression Scale (HADS), and RAND-36. At baseline and follow-up, a clinical assessment of opioid use disorder is performed.

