### Eligibility criteria {10}

Inclusion criteria are age ≥ 18 years with long-term (> 3 months) non-malignant pain and long-term prescribed opioid consumption (> 3 months) with a participant and/or prescribing doctor calling for tapering of opioids. All pain classes will be included, i.e., nociceptive pain (both somatic (musculoskeletal) and visceral), neuropathic pain, and nociplastic pain. Tapering of opioids is thus proposed without regard to pain mechanism or diagnoses. The requirement regarding functioning is (1) that a participant is able to absorb and retain information and is thus able to make an informed decision and (2) is at a functional level that permits outpatient visits.

Exclusion criteria at baseline are repeated intake of non-prescribed opioids or other illegal drugs, refusal to perform drug screening, prescription periods shorter than 3 months, and perceived medical risks of waiting with tapering of opioids (e.g., raising opioid doses after acute pancreatitis caused by excessive alcohol intake or kidney disease stage 4–5 in combination with excessive alcohol intake and high doses of opioids). The occurrence of substance use disorder without the use of illicit drugs is not an exclusion criterion.

Exclusion criteria were selected as a safety option to the physician at baseline visit when estimating the individual risks of the ongoing opioid treatment with regard to both overdose and development of dependence whenever a short duration (< 3 months) of treatment has occurred.

Otherwise, eligible participants who chose to not be included in the Swedish Quality Registry for Pain Rehabilitation (SQRP) will also be excluded.

The intervention will be carried out by physicians and nurses employed at tertiary pain clinics.

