#### Primary outcomes

Consumption of opioids, measured as MME, will be evaluated using data extracted from the Swedish drug register of the National Board of Health and Welfare (SDPR) where registration of all withdrawals of prescribed drugs is made. MME will be calculated using these data. At all baseline visits and 12-month follow-ups, the MME will be calculated for the preceding 90 days, but at 4 months after the intervention, the dose will be calculated for the preceding 30 days as the intervention is estimated to last approximately 3 months.

Self-reported opioid consumption will also be evaluated and reported in MME. Calculation of morphine equivalent dose will be performed with conversion factors used in Cochrane review [7].

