### Sample size {14}

A “responder” to treatment is a participant who experiences at least a 50% reduction in opioid consumption [28]. Estimation of sample size was based on an effect size of 0.5 (Cohen’s *d*) 80% power, *α* = 0.05, and drop-off at 10%. The results from the calculation indicated the need for 70 individuals in each group.

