## Statistical methods

### Statistical methods for primary and secondary outcomes {20a}

All statistical analyses will be performed with the SPSS software (version 25, IBM Inc). Continuous data will be expressed by means, standard deviation and 95% confidence interval, and categorical data in numbers and percentages.

The intervention arm (tapering opioids) will be compared with control (waiting list) for primary and secondary outcomes at 4 months of follow-up. Statistical analysis of differences between groups will be performed per protocol (attending follow-up 4 months after the start of the intervention and attending second baseline visit in controls) with a paired *t*-test regarding the primary outcome and a Wilcoxon signed-rank test regarding secondary outcomes.

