## Abbreviations

CPAQ-8: Chronic Pain Acceptance Questionnaire
HADS: Hospital Anxiety and Depression Scale
MME: Milligram morphine equivalent dose per day
NPRS: Numeric Pain Rating Scale
PCS: Pain Catastrophizing Scale
PEth: Phosphatidylethanol 16:0/18:1
RCT: Randomized controlled trial
SPDR: Swedish Prescribed Drug Register
SQRP: Swedish Quality Registry for Pain Rehabilitation
SUD: Substance use disorder
TSK: Tampa Scale of Kinesiophobia

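### The taper, hypothesis and responder definition are relative to each person's own dose, but the primary test is on absolute MME, so it does not evaluate the 50% target and its power rests on an unstated dose spread

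*Protocol article*

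**What the plan says.** All references are to the protocol article.

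**Relative to the person's own dose**
- Intervention description {11a}: "the participant is advised to decrease the dosage with approximately 5–10% from starting dose every week".
- Objectives {7}: the research hypothesis is a fall in intake of at least 50%, together with superiority over controls in dispensed opioids.
- Sample size {14}: a responder is "a participant who experiences at least a 50% reduction in opioid consumption".
- Methods for additional analyses {20b}: retention at 12 months is calculated as percent change.

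**Absolute**
- Primary outcomes, under Outcomes {12}: "Consumption of opioids, measured as MME, will be evaluated using data extracted from the Swedish drug register". The abbreviation list has "MME: Milligram morphine equivalent dose per day", and the abstract says "individual mean daily opioid dose in morphine equivalents will be calculated at three time points".
- Statistical methods {20a}: "The intervention arm (tapering opioids) will be compared with control (waiting list) for primary and secondary outcomes at 4 months of follow-up", "with a paired *t*-test regarding the primary outcome and a Wilcoxon signed-rank test regarding secondary outcomes". That section names no percentage, log scale, baseline adjustment or responder comparison.

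**Dose spread**
- Eligibility criteria {10} set a duration, "long-term prescribed opioid consumption (> 3 months", but no lower or upper daily dose.
- The information given before randomization foresees doses above 100 mg and answers them with advice, not exclusion.
- Sequence generation {16a} describes 1:1 allocation and no stratification by dose.
- Sample size {14} gives Cohen's d = 0.5 with no SD and no mg difference.

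**The concern.** If a taper removes a fraction of each person's dose, its effect in mg is that fraction times the starting dose. A mean difference in mg then weights participants by their starting dose, and its standardised size depends on the spread of starting doses as well as on how well the taper works. Two things are at stake. First, the primary result would not answer the question posed under Objectives {7}, whether intake falls by half. Second, the planned 80% power is not attached to any relative reduction: the same halving can be over- or under-powered according to who enrols. Separately, a paired t-test has no pairs to work on when the two arms contain different people.

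**Working it through.** **1. The plan's own figure.** Inputs from Sample size {14}: d = 0.5, power 80%, α = 0.05 (two-sided assumed, as sidedness is not stated), drop-off 10%.

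n per arm = 2 × (1.960 + 0.842)² / 0.5² = 62.8, rounded up to 63; 63 / 0.9 = 70. The stated 70 per group is reproduced. It is the figure for two independent groups; a truly paired design at the same d would need only 34 pairs. The sizing and the named test therefore do not match.

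**2. A pure halving on 4-month mg.** The documents give no dose distribution. Assume lognormal doses with mean m and coefficient of variation CV in the control arm, and every dose halved in the taper arm.

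- Difference in means = 0.5m.
- SDs are CV·m and 0.5·CV·m, so pooled SD = CV·m·√((1 + 0.25)/2) = 0.791·CV·m.
- d = 0.5 / (0.791·CV).
- Share of all mg held by the top tenth = Φ(σ − 1.2816), with σ² = ln(1 + CV²).

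| CV | d | Power, 63 per arm | Top tenth's share of mg |
|---|---|---|---|
| 0.6 | 1.05 | about 100% | 23% |
| 1.0 | 0.63 | 94% | 33% |
| 1.5 | 0.42 | 65% | 42% |
| 2.0 | 0.32 | 42% | 49% |

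Setting d = 0.5 gives CV = 0.5 / (0.791 × 0.5) = 1.26. The planned 80% thus corresponds to a halving only if doses happen to have that spread.

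**3. Does another mg analysis cure it?** Simulation with assumed inputs: 63 per arm, 20% of tapered participants at zero, month-to-month log-SD 0.5, 2,000 runs. Power at CV 1.0 / 1.5 / 2.0:

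| Analysis | Mean cut 50% | Mean cut 30% |
|---|---|---|
| 4-month mg | 0.84 / 0.61 / 0.46 | 0.33 / 0.22 / 0.18 |
| mg change | 0.97 / 0.88 / 0.78 | 0.60 / 0.46 / 0.37 |
| Baseline-adjusted mg | 0.98 / 0.92 / 0.84 | 0.61 / 0.49 / 0.42 |
| Percent of own baseline (capped at 200%) | 1.00 / 1.00 / 1.00 | 0.91 / 0.90 / 0.89 |

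Month-to-month noise matters. With 30% of tapered participants at zero and a 50% mean cut, baseline-adjusted mg has power 1.00 / 0.98 / 0.95 at log-SD 0.3, but 0.76 / 0.63 / 0.56 at log-SD 0.8. With less noise still (remaining-dose SD of 0.35 in the taper arm and 0.25 in control, independent of baseline), mg change keeps at least 0.95 for a 50% cut even at CV 2.0. Percent of own baseline, analysed without a cap, had power at least equal to each mg analysis in every setting with a true effect.

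**4. The dispensing window.** Primary outcomes counts 90 days of dispensing at baseline and 30 days at 4 months. Suppose a stable control collects 90-day supplies (an assumption). A 30-day window catches a collection one time in three and then records 300% of baseline; otherwise it records 0%. The mean is (1/3) × 300% = 100%, which is unbiased but lumpy. A cap at 200% would turn it into (1/3) × 200% = 67%. In simulation, 90-day supplies in half or all controls lowered the capped control mean to 83% or 66% and raised the type I error to about 30–80%; the uncapped percentage stayed near nominal.

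**The case against.** **Milligrams are a legitimate quantity.** The objective speaks of dispensed opioids, and the protocol ties overdose risk to an absolute level of 100 mg. Giving heavier users more weight can be defended. This stands, and is why the mg result should be kept. It does not make the mg test a test of the 50% hypothesis.

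**A few high-dose participants decide the result.** A reader might infer this, but the documents do not support it, because they report no dose distribution. At CV 0.6 the top tenth hold about 23% of the mg, and with low month-to-month noise a 50% cut is detected on any scale. Domination by high doses is a possibility under strong skew only.

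**The test may be on change.** Statistical methods {20a} leave open whether 4-month MME or change in MME is compared. Change, or adjustment for baseline, recovers much of the loss when month-to-month noise is low. This also stands: the lowest power figures belong to unadjusted 4-month mg. Both readings remain in mg, however, and both still depend on dose spread.

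**The scale could be left to an analysis plan.** Finer detail could. But the article itself fixes the outcome unit, the time point and the test, and what it fixes is on a different scale from its hypothesis.

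**Percentages bring their own trouble.** They are unstable at low baseline doses and affected by the unequal windows. True; the fix has to deal with both.

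**Conclusion.** The mismatch of scale is in the text and needs no assumption: taper, hypothesis, responder definition and 12-month analysis are relative, while the primary test is on mg per day. The named paired test does not fit two independent arms. The 50% hypothesis is not evaluated by the primary analysis, and d = 0.5 is linked neither to it nor to any SD.

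The size of the power problem is conditional. It rests on lognormal doses, 63 analysed per arm and an assumed CV. For a pure halving on 4-month mg, power runs from about 100% at CV 0.6 to 42% at CV 2.0, against the planned 80%. The loss is serious with strong skew, with a smaller relative reduction, or with high month-to-month noise, and it is partly recovered by change or baseline adjustment. The point concerns the analysis only and implies nothing about the taper rate or the doses admitted. It should be corrected.

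**What to change.** Make these changes before register data are extracted. The article says extraction takes place once all follow-ups are closed, and no interim analysis is planned.

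1. **Primary outcomes and Statistical methods {20a}:** define the primary variable as 4-month register MME as a percentage of the participant's own baseline register MME. Replace the paired t-test with an unequal-variance two-sample test, and report the difference in mean percent with its 95% CI. Do not cap the percentage, for the reason shown in step 4 of the working.
2. **Very low baseline doses:** handle them by a pre-specified sensitivity analysis.
3. **Dispensing window:** use the same window at baseline and 4 months, or pre-specify a sensitivity analysis to its length.
4. **Supportive result:** report the baseline-adjusted difference in mg.
5. **Sample size {14}:** restate it in percent units, giving the target difference and the assumed SD.

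The cost is changed wording and a redone sample-size statement; no new data are needed. The downside is that percentages are noisier at low baseline doses, and the mg result becomes supportive.

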#### Follow-up visit at 4 months

Four months after initiation, a visit with a study physician and nurse is performed:
Obstacles and successes are discussed. Personal experiences and conclusions are important topics of this meeting.In case of the remaining daily intake of opioids and if the participant is interested in further support in tapering, this demand is met if considered possible within a well-defined timeframe.Assessment of non-narcotic medications for the treatment of long-term pain including dosage and suggested treatment period.Assessment of further needs for the participant, e.g., whether participation in interdisciplinary multi-modal pain rehabilitation in a group is called for or other individual approaches of rehabilitation at the primary health care level.Clinical assessment as to whether any interventions from opioid disorder care are warranted.Drug screening including B-PEth is performed.The visit and outcome of the intervention complete with recommendations regarding future prescription are summarized and communicated to the physician. The recommendations are created in collaboration with the participant.

### Criteria for discontinuing or modifying allocated interventions {11b}

Non-compliance to the treatment plan or drug screening showing evidence of a drug not prescribed calls for attention from a physician. Additional screening for a multiple of drugs available on the illicit market may be performed. Renewal of the treatment plan is offered, and the participant may be retained in the study and final analysis.

If the treatment plan, despite this, is not followed, the participant is referred to an addiction care center and excluded from the final analysis.

There are no restrictions due to concomitant care and interventions during the trial.

### Strategies to improve adherence to interventions {11c}

A motivational approach is used in the consultation at the start of tapering. Participant’s worries, thoughts, and expectations are explored. Firstly, the patient’s perspective of opioid use is considered. Time is spent on reflections and concerns relating to the tapering process. Increased pain during tapering is a well-known fear. The patient’s history and experience of potential side effects are linked with known risks of opioids in an individualized manner, and the patient is reassured of the possibility to contact nursing staff on office hours.

Compliance will be monitored mainly by telephone support by an assigned study nurse once a week in the beginning of tapering. It is optional to attend in person. Distribution of opioids once a week may occur by decision from the physician or if preferred. Monitoring of symptoms related to abstinence or other symptoms is the main target as well as monitoring the willingness to continue the tapering plan. Participants will also be advised to take contact if problematic symptoms prevail.

Once a week, physicians and nurses meet to discuss obstacles in tapering. The main strategy to deal with increased symptoms is to change the speed of tapering and make adjustments with non-narcotic drugs (i.e., NSAID, paracetamol, alimemazine, amitriptyline, duloxetine, gabapentin).

